**Aim 1:** Evaluate the difference between HOPS-ST and TAU-WL on improvement in proximal outcomes (organization skills, homework performance) and distal outcomes (academic performance) at post-treatment (4-months after baseline) and explore the intervention’s sustainability (6 and 12-months after baseline). This aim will enable our team to determine the effectiveness of HOPS when provided by school professionals. We hypothesize that students in the HOPS-ST group will demonstrate significantly fewer OTMP skills deficits and homework problems and will show significantly better academic performance at post-treatment compared to students in TAU-WL. In addition, we expect the benefits of HOPS-ST to be maintained at follow-up.**Aim 2:** Examine the effectiveness of HOPS-RT in relation to TAU-WL. This aim will enable our team to replicate the findings of the [name] et al. [4] trial. We hypothesize that students in the HOPS-RT group will demonstrate significantly fewer OTMP skills deficits and homework problems and would show significantly better academic performance at post-treatment compared to students in TAU-WL. In addition, we expect the benefits of HOPS-ST to be maintained at follow-up.**Aim 3:** Explore differences in effect for HOPS-ST and HOPS-RT at post-treatment and follow-up.**Aim 4:** Explore mechanisms of action, specifically whether improvements in OTMP skills and homework performance mediate the effect of HOPS on improvements in academic performance.**Aim 5:** Explore whether student grade level, severity of organization problems, severity of ADHD, oppositional defiant behavior, and internalizing symptoms, and student medication status at baseline moderate the effect of HOPS on outcomes.**Aim 6:** Explore the extent to which treatment fidelity, student engagement, parent engagement, teacher engagement, and provider-student working alliance predicts outcomes for students in HOPS.**Aim 7:** Estimate the cost of providing HOPS under authentic practice conditions in schools.

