#### Concealment.

Given that the study is a pragmatic trial being conducted under real-world conditions, no attempt will be made to conceal treatment assignment from caregivers, students, teachers, and intervention providers. In addition, study team members will be fully aware of treatment assignment.

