#### Collection of outcome data.

Outcome data for students in HOPS and TAU-WL will be collected at baseline and post-treatment (about 4 months after baseline). Follow-up data will be collected 6 months after baseline for students assigned to the HOPS condition. In addition, follow-up data will be collected 12 months after baseline for students in HOPS who remain in their school of enrollment the following school year. We will not collect 6-month and 12-month follow-up data for students in TAU-WL because of ethical concerns about further delaying the delivery of HOPS to those in the control group. However, we will collect post-treatment outcome data after students in the TAU/WL condition receive the HOPS program. Treatment fidelity, student engagement, and parent engagement will be assessed for participants in the HOPS condition during the intervention period. Provider-student working alliance will be assessed after the intervention period. Severity of organization problems, ADHD symptoms, disruptive behavior symptoms, and anxiety symptoms, as well as school organizational factors that may contribute to intervention implementation, will be assessed at baseline. (See Fig 3 for the study plan and flow diagram and see Fig 1 for a list of measures and the timelines for administering measures).

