### Recruitment

Two primary methods will be used to recruit schools. First, emails will be sent to the principals of schools serving students in grades 6–8 located in the large metropolitan area in which the study will be conducted. The selection of schools will be inclusive of districts across the region to achieve balance across subsidized lunch rate levels of the schools (low [0%−30%], middle [31%−60%], and high [61%−100%]). In addition, there will be an intentional effort to recruit schools in urban, suburban, and rural areas. Second, emails will be sent to principals of schools from districts in which we have previously conducted research or those referred to us by school administrators or other researchers. Approval will be obtained from the school principal, school superintendent, and school board (as necessary) prior to conducting research in the school. In addition, principals will be asked to identify one or more school providers to implement the HOPS intervention. School provider(s) must provide consent to participate in the study for the school to be enrolled in the study. Once all approvals and consents are obtained from school professionals, the school will be randomly assigned to a study condition (HOPS vs. TAU/WL).

Students will be referred to the study by their classroom (general education) teachers. School principals will identify the specific strategies to be used in convening teachers, informing them about the study, and obtaining referrals. Teachers will be informed that referral of a student to the study indicates their willingness to complete forms for outcome evaluation. The pool of teachers selected for inclusion in the referral process will be asked to nominate students from their general education classroom: (a) who are struggling the most with OTMP skills, (b) whose OTMP skill deficits interfere with their academic performance, and (c) who have at least one caregiver who speaks English. Each teacher who agrees to participate will complete a nomination form for each referred student for the purpose of determining student eligibility.

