### Outcome measures – Proximal and distal

The *Children’s Organizational Skills Scale – Parent and Teacher versions (COSS-P, COSS-T)* will be used to assess changes in OTMP functioning at home and school. COSS Total scores (26 items for COSS-P, 28 for COSS-T) have strong construct and discriminant validity [23] and treatment sensitivity [4]. Each item is rated on a 4-point scale. The total score will be used in analyses, with higher scores being less favorable.

The *Homework Problem Checklist (HPC)* is a 20-item caregiver-report measure that indicates the frequency of child homework problems. The HPC has been shown to have strong construct validity [24] and treatment sensitivity [4]. Each item is rated on a 4-point scale. The total score will be used in analyses with higher scores indicating more problems.

The *Homework Performance Questionnaire – Teacher version (HPQ-T)* assesses students’ homework behavior during the past 4 weeks. Each item is rated on a 7-point scale indicating how often each behavior occurs, with higher scores indicating better performance. The 17-item General factor that assesses overall homework competence has strong construct validity [25] and will be used in analyses.

The *Academic Proficiency Scale (APS)* is a teacher-report measure assessing proficiency in six academic subjects. Each item is rated on a 5-point scale (1 = well below standard expected at this time of year; 3=at standard; 5 = well above standard). This measure has high internal consistency [8] and strong treatment sensitivity [5]. The mean item score will be used in analyses, with higher scores indicating better performance.

Student *academic report card grades* will be used to examine the impact of HOPS vs. TAU/WL on academic performance. Student grades will be recorded for the last marking period of the year prior to enrollment (baseline), the year of enrollment (post-treatment), and the year following enrollment (follow-up). Grades will be harmonized across participating school districts to a uniform grading scale (ranging from a low of 1 to a high of 4). A composite academic grade score will be computed for each student based on their grades in math and reading/language arts (possible range = 1–4). Higher scores indicate better outcomes.

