#### Analyses for Aims 1–3: Evaluation of HOPS vs. TAU/WL and comparison of HOPS-ST to HOPS-RT.

*Hypothesis 1:* Students in HOPS-ST will demonstrate significantly fewer OTMP skills deficits and homework problems and will show significantly better academic performance at post-treatment compared to students in TAU-WL*Hypothesis 2:* Students in HOPS-RT will demonstrate significantly fewer OTMP skills deficits and homework problems and will show significantly better academic performance at post-treatment compared to students in TAU-WL.*Exploratory:* Examine whether the effects of HOPS-ST and HOPS-RT differ at post-treatment and follow-up.

A linear mixed-effects modeling approach will be used to examine intervention effects at post-treatment. An intent-to-treat approach to data analysis will be applied, including all children with baseline data in the analytic model. Under this approach, we will examine differences between students in HOPS (for HOPS-ST and HOPS-RT separately) vs. TAU-WL (as well as for students in HOPS-ST vs. HOPS-RT) by fitting a multilevel model in which students are nested within schools. In addition to including an indicator variable for the treatment condition, we will include covariates that explain variation at the student and school levels. To explore the sustainability of the intervention effect, we will examine how both means and slopes (rates of change) vary from baseline to 6-month and 12-month follow-up using regression analyses. Changes in mean and slope reflect variations in the magnitude of effect and pace of change during different phases of the study.

Because the efficacy of HOPS will be evaluated on three different domains of outcome measures (organizational skills, homework performance, academic achievement), we will use a Bonferroni-adjusted significance level to correct for multiple comparisons within each domain. As a result, the significance level will be adjusted to.025 per domain for the two measures of organizational skills (COSS-P, COSS-T), the two measures of homework performance (HPC, HPQ-T), and the two measures of academic achievement (APS, academic grades).

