#### Analyses for Aim 4: Mediation.

We will use structural equation modeling (SEM) to conduct mediation analyses [40] to explre if the effect of HOPS on academic performance works through improved organizational skills. SEM approaches allow us to explore individual and multiple mediator relationships by positing a path model for each mediator variable. Applying this framework, the total intervention effect is decomposed into two components: natural direct effect (NDE = the effect of HOPS on students’ academic performance without mediation), and the natural indirect effect (NIE = the effect of HOPS that seems to proceed through improved organization skills). As a result, total effect of HOPS = NDE + NIE and a significant NIE implies that the effect of HOPS on academic performance works through improved organizational skills [41].

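### Aim 4 reads a significant indirect effect as mechanism, but for teacher-rated mediator and teacher-rated outcome shared rater error plus an arm difference in the mediator rating can produce one with no true path

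*Protocol article*

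**What the plan says.** Aim 4 (Study purpose and aims) is exploratory. It asks "whether improvements in OTMP skills and homework performance mediate the effect of HOPS on improvements in academic performance". The section Analyses for Aim 4: Mediation splits the total effect into a natural direct effect (NDE) and an NIE by structural equation modelling. It defines the NIE in cautious terms, then closes with an unconditional rule: "a significant NIE implies that the effect of HOPS on academic performance works through improved organizational skills". It does not say which informant supplies the mediator or the outcome.

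Other sections fix what those can be:

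- **Mediator.** Organizational skills are scored by caregiver (COSS-P) and teacher (COSS-T). Homework is scored by caregiver (HPC) and teacher (HPQ-T).
- **Outcome.** Academic performance is the APS, which "is a teacher-report measure assessing proficiency in six academic subjects", and report card grades (Outcome measures).
- **Rater.** Under Recruitment, teachers are told that "referral of a student to the study indicates their willingness to complete forms for outcome evaluation".
- **Blinding.** Under Concealment, "no attempt will be made to conceal treatment assignment from caregivers, students, teachers, and intervention providers".
- **Timing.** Under Collection of outcome data, "Outcome data for students in HOPS and TAU-WL will be collected at baseline and post-treatment (about 4 months after baseline"). The control group has no 6- or 12-month follow-up.

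**The concern.** Randomization protects the path from HOPS to the mediator. It does not protect the path from mediator to outcome, which is an observational association within arms. If one teacher completes COSS-T and APS at the same wave, a general good or bad impression of the student enters both scores. The model has no means of separating that from a causal path, and the rule turns a significant product of paths into a statement about mechanism.

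At stake is the theory of change. The Discussion says that the study will identify how the intervention exerts its effect. A same-teacher result could support that statement when organizational skills have no influence on achievement at all.

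**Working it through.** The mediation section gives no figure to reproduce, so the check asks how often the rule would fire when the true mediator-to-outcome effect is zero.

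**Inputs from the protocol article:** 122 analysed students; 30 schools, 20 HOPS and 10 TAU; ICC 0.04 (power paragraph); teacher-rated effects of 0.53 and 0.55 SD in the prior large trial (Prior research on HOPS program). At 2:1, 122 students are about 81 and 41.

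**Assumptions:** residual correlation ρ between mediator and outcome ratings from shared rater error (not in the document, so a range is shown); unit variances; NIE called significant when both paths are significant at two-sided 0.05 (joint test).

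**Step 1. Size of the false effect.** Let M = a·T + e_M and Y = e_Y, with corr(e_M, e_Y) = ρ. Regressing Y on T and M gives an expected slope on M of b = ρ, so NIE = a·ρ. For a = 0.53 this is 0.53 × 0.2 = 0.11 SD and 0.53 × 0.3 = 0.16 SD. The true total effect here is zero, so the model reports an offsetting NDE of −a·ρ. The rule looks only at the NIE.

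**Step 2. How often it is significant.**

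- a-path: SE = √(1/81 + 1/41) = 0.192; 0.53/0.192 = 2.76; probability of significance Φ(2.76 − 1.98) = 0.78.
- b-path: SE = √((1 − ρ²)/119).

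| ρ | SE(b) | ρ/SE(b) | P(b signif.) | × 0.78 | Simulated, no clustering, a = 0.53 | Simulated, clustered, a = 0.55 |
|---|---|---|---|---|---|---|
| 0 | 0.092 | 0 | 0.05 | 0.04 | 4% | 4.2% |
| 0.2 | 0.090 | 2.23 | 0.60 | 0.47 | 48% | 41.2% |
| 0.3 | 0.087 | 3.43 | 0.93 | 0.73 | 73% | 65.2% |
| 0.4 | 0.084 | 4.76 | 1.00 | 0.78 | 78% | not run |

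The clustered runs use 30 schools at 20:10, ICC 0.04 and cluster-robust standard errors. A Sobel test in those runs gives lower rates: 25.5% at ρ = 0.2 and 49.6% at 0.3.

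**Step 3. No arm difference in the rated mediator.** With a = 0 and ρ = 0.3 the hand figure is 0.05 × 0.93 = 0.046. The clustered simulation gives 5.3% (joint) and 2.5% (Sobel), mean NIE 0.00.

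**Step 4. No real HOPS effect, but unblinded teachers shift both ratings.** At ρ = 0.3, a shift of 0.3 SD gives 27.2% (NIE 0.09) and a shift of 0.5 SD gives 58.8% (NIE 0.14). With a 0.5 SD shift and ρ = 0, the rate is 3.4%. A rating shift by itself does not create the b-path.

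**Step 5. Baseline mediator and outcome as covariates** (unclustered, a = 0.53, assumed trait stability 0.6). At ρ = 0.2 and 0.3, the rates are about 7% and 8% if the halo is fully stable from baseline to post-treatment. They are about 28% and 58% if its stability is 0.8. Adjustment helps only as far as it lowers the correlation that remains: with clustering, a = 0.53 and covariates explaining R² = 0.60 (the article's own figure), remaining correlations of 0, 0.1, 0.2 and 0.3 give 5%, 19%, 56% and 89%.

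**The case against.** The other side has several fair points.

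- **Shared rater error alone does not suffice.** A reader might infer that it does. Step 3 shows otherwise: without an arm difference in the rated mediator the rate stays near 5%. This stands.
- **The plan does not claim proof, and the aim is exploratory.** A reader might take the rule as a claim of proven mechanism on which the trial rests. The document says *implies*, it is cautious earlier in the same section, and the effectiveness hypotheses belong to Aims 1 and 2. This stands and limits the weight of the point. It does not make the closing rule correct.
- **The plan does not prescribe the same-teacher pair.** It names no informant, and nothing says that one teacher must complete both scales. COSS-P with APS or with grades is available and does not share a rater form. So all of Aim 4 is not undermined. But the rule as written covers a COSS-T with APS result like any other, and nothing excludes it.
- **Grades are not necessarily concurrent.** They come from the last marking period of the enrolment year, so they may follow the mediator rating. They are not a clean later comparison either, because some TAU/WL students may receive HOPS that spring. COSS-T may also share a rater with grades if that teacher grades the student.
- **The correlations are assumed, and baseline adjustment may remove most of the problem.** True if the halo is nearly constant. The document gives no figure for its stability.
- **Caregiver mediators are not clearly better as primary.** Caregivers are also unblinded and receive consultations, and COSS-P and HPC reflect behaviour seen at home. This stands, so the fix does not make them primary.

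Covariates and clustering in the mediation model are details that an article may leave to the full plan; their absence is not criticised here.

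**Conclusion.** The concern holds for teacher-teacher pairs: COSS-T or HPQ-T as mediator with APS as outcome. For these, a significant NIE does not imply that HOPS works through the mediator, because shared rater error together with an arm difference in the mediator rating can produce it. The spurious NIE is about 0.11 SD at ρ = 0.2 and 0.16 SD at ρ = 0.3. Those sizes and the unadjusted error rates rest on an assumed ρ, an arm difference borrowed from the prior trial, the joint test and no baseline covariates; the adjusted rates rest further on the assumed halo stability. The documents do not settle where in that range the trial would fall, and they do not show that the false result will occur. They do show that the rule carries no safeguard against it.

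Separately, Aim 4 names homework performance as a mediator while the stated purpose, NIE definition and rule of the analysis section name only organizational skills. That section does allow for several mediators, so this is a matter of wording.

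**What to change.** In Analyses for Aim 4: Mediation:

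1. Replace *implies* with *is consistent with*.
2. State that no conclusion on mechanism will be drawn from a same-teacher pair alone. Beside any such NIE, report the cross-informant NIE (COSS-P or HPC as mediator, with APS and with grades as outcome), adjusted for baseline mediator and outcome.
3. Report how large a mediator-outcome residual correlation would remove the NIE.
4. Name homework performance as a mediator, to match Aim 4.

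All the measures are already collected, so the cost is wording and a little more analysis. The downside is that ratings by different informants correlate less, so a true indirect effect will be harder to confirm. Cross-informant pairing removes shared rater error but not other mediator-outcome confounding, which is why items 1 and 3 are needed as well.

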#### Analyses for Aim 5: Effect modification.

Our plan is to explore the moderating effect of severity of organization problems, ADHD, oppositional defiant behavior, and internalizing symptoms, ADHD medication status, as well as socioeconomic level (i.e., caregiver level of education, Area Deprivation Index) at baseline on the effectiveness of HOPS. These moderators will first be examined individually in the previously described mixed effects models. Baseline scores on the moderators that are continuous variables will be centered in relation to the group-mean within each school. The moderators will be examined as a moderator by treatment group interaction term in each of the multi-level models. Significant interaction effects for both continuous and discrete variables imply moderation effects, where the magnitude and sign of the estimated coefficients reflect the moderated change in treatment effect. Following the analytic plan used by [name] and colleagues [4], significant interaction effects among the continuous moderators will be examined at the 25^th^, 50^th^, and 75^th^ percentile levels of the moderator. For the discrete variable (medication status), we will compare treatment effects for students on and off medication at baseline to assess the magnitude of the moderating effects. In addition, we will examine the combined effect of multiple moderators. This will be done by incorporating multiple interaction terms and several higher order interaction effects in the mixed effects models (see analytic plan for Aims 1–3). The purpose of these analyses is to explore whether the inclusion and exclusion of specific moderator variables augment or attenuate the moderating effect of different variables.

Similar to [name] and colleagues [4], we will formally test the significance of moderator effects using the models described for Aims 1–3. We will also examine the proportion of variation in the outcomes that is explained by the moderators, given by the magnitude of the adjusted R^2^ values. In addition, we will report the 95% confidence intervals for the moderator by treatment group interaction, because confidence intervals provide more precise information about the magnitude of the moderator effect [42].

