### Research settings

The study will be conducted in Philadelphia, PA greater metropolitan region. Our team will purposely recruit schools that are highly diverse in subsidized lunch rates of the schools and racial and ethnic composition of the students to maximize generalizability. Our team will attempt to recruit schools with varying levels of urbanicity (i.e., rural, suburban, and urban). We expect the racial and ethnic minority composition across schools to range from 15% to 99% and subsidized lunch rates to range from 15% to 100%. For each school, we plan on recruiting one or two school providers to implement the HOPS intervention.

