Power calculations were based on the following design parameters: *N = 30* schools (20 assigned to HOPS, 10 assigned to TAU); ICC = 0.04 (based on [4]); α=0.025  (reflecting the Bonferroni corrected significance level to accommodate multiple testing of two outcomes for each outcome domain); and $R^{\text{2}}=\text{0}.\text{6}\text{0}$ at the student and school level (which is the proportion of variation in outcomes explained by student and school-level covariates). Based on initial projections, we expected to enroll 8 students per school for a total of 240 participants (216 with 15% attrition), which would be sufficient to identify a minimal detectable effect size (MDES) of 0.41. Because of recruitment challenges primarily due to barriers related to the COVID-19 pandemic, we adjusted these projections to an average of 4.5 students/school for 30 schools for a total of 135 participants (122 with attrition). This sample size will result in a MDES of 0.48 with adequate power (80%). Based on prior research by [name] and colleagues [4], the MDES for primary outcomes in our study is well within the range of expected effect sizes.

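### School-mean centering of the continuous moderators leaves Aim 5 unable to detect between-school moderation, which matters most for the Area Deprivation Index

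*Protocol article*

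**What the plan says.** The section Analyses for Aim 5 lists as moderators the severity of organization problems, ADHD, oppositional and internalizing symptoms, medication status, and "socioeconomic level (i.e., caregiver level of education, Area Deprivation Index) at baseline on the effectiveness of HOPS". For the continuous ones it fixes the coding: "Baseline scores on the moderators that are continuous variables will be centered in relation to the group-mean within each school". The test is then described: "The moderators will be examined as a moderator by treatment group interaction term in each of the multi-level models". For follow-up, "significant interaction effects among the continuous moderators will be examined at the" 25th, 50th and 75th percentiles of the moderator. The text does not say whether these are percentiles of the raw or the centered score. Neither the school mean of a moderator nor its interaction with treatment is mentioned.

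Two other places set the context. The power paragraph under Analyses for Aims 1–3 says the team "adjusted these projections to an average of 4.5 students/school for 30 schools", giving 135 students, or 122 after attrition. Research settings says schools are recruited on purpose to be diverse, with "subsidized lunch rates to range from 15% to 100" percent.

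**The concern.** HOPS versus TAU/WL is assigned by school. Once a moderator is replaced by its deviation from the school mean, it averages zero in every school. Its interaction with treatment can then show only whether the HOPS effect differs between higher- and lower-scoring students of the same school. It cannot show whether HOPS works differently in schools whose enrolled students are, on average, more severe or more deprived. Two students with the same raw score in different schools receive different values, and each value depends on which four or five students happened to enroll.

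Family socioeconomic level is named as a possible effect modifier in the Abstract, in Conceptual framework of HOPS and in the Aim 5 analysis section. The Discussion counts neighborhood disadvantage among the study's strengths. If deprivation varies largely between schools, the planned test discards much of the information the sample holds on it, and a null result could come from the coding rather than from the absence of moderation.

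**Working it through.** **Cluster size.** 135/30 = 4.5 students per school, as stated; after attrition 122/30 = 4.07. For contrast, the prior large trial cited in the Introduction had 280/7 = 40 per school.

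**Variance kept.** With moderator ICC ρ and m students per school, the deviation from the school mean keeps (1 − ρ)(1 − 1/m) of the variance. At m = 4.5, 1 − 1/m = 0.778, so 22% is lost even if schools do not differ at all (ρ = 0). At m = 40 that part would be 1/40 = 2.5%.

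**Effect on the test.** A simulation (3,000 runs per setting) used:
- 30 schools, split 20 HOPS and 10 TAU/WL, with 4 or 5 students each and the two HOPS provider groups pooled;
- residual variance from the protocol's R² = 0.60 and outcome ICC = 0.04: 0.04 × 0.40 = 0.016 between schools and 0.96 × 0.40 = 0.384 within;
- a random-intercept model, tested two-sided at 0.05;
- an assumed interaction of 0.25 per SD of the moderator, equal within and between schools.

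| Assumed moderator ICC | Variance kept (m = 4.5) | SE ratio, school-mean to grand-mean centering | Power, grand-mean | Power, school-mean |
|---|---|---|---|---|
| 0.04 | 0.96 × 0.778 = 0.75 | 0.133/0.117 = 1.14 | 56% | 46% |
| 0.10 | 0.90 × 0.778 = 0.70 | 0.139/0.121 = 1.15 | 55% | 45% |
| 0.30 | 0.70 × 0.778 = 0.54 | 0.159/0.124 = 1.28 | 54% | 37% |
| 0.50 | 0.50 × 0.778 = 0.39 | 0.185/0.127 = 1.46 | 49% | 26% |
| 0.70 | 0.30 × 0.778 = 0.23 | 0.235/0.132 = 1.78 | 47% | 18% |

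The school-centered interaction averaged 0.24 to 0.25 against a true 0.25, so it is unbiased for the within-school slope. The cost is in precision.

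**Moderation acting only between schools** (0.25, ICC 0.50). The school-centered interaction averaged 0.006 and rejected in 5.2% of runs, which is the null rate. Adding the school mean and school mean × treatment gave a between-school estimate of 0.20 with 22% power. The shortfall from 0.25 is what a mean of 4.5 students implies: its reliability is 0.5/(0.5 + 0.5/4.5) = 0.82, and 0.82 × 0.25 = 0.20. Where the within- and between-school slopes were equal, adding the two terms left the within-school estimate, its SE and its power unchanged in every row of the table.

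**The case against.** School-mean centering is a recognised choice for a student-level moderator crossed with a school-level treatment, and a within-school question is coherent. The Area Deprivation Index is recorded per family. Aim 5 is exploratory, and its statement under Study purpose and aims does not list socioeconomic level. For the HOPS-ST versus HOPS-RT contrast, where students are randomized within HOPS schools, within-school centering is natural. Grand-mean centering would blend the two kinds of moderation. Power is limited under any coding. All of this stands, and it rules out calling the rule an error or replacing it outright.

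A reader might infer more than the document supports:
- *That the test uses students' rank.* It does not; the centered score is a deviation in scale units.
- *That Aim 5 is meant to study differences between schools.* The document lists student and family moderators, and gives generalizability as the reason for school diversity.
- *That centering leaves the main HOPS effect unadjusted for chance imbalance.* Aim 5 concerns an interaction. Imbalance is addressed by stratification on subsidized lunch, by adding baseline variables that differ between groups, and by student- and school-level covariates in the Aims 1–3 model.
- *That the percentiles are certainly those of the centered score.* The text leaves this open.

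It can also be said that a condensed article leaves the model equation to an analysis plan not shown here. The article does mention unspecified school-level covariates and higher-order interactions. But covariate main effects do not test moderation, the higher-order interactions are described as combining several moderators, and the centering rule is stated outright. No stated term recovers the between-school part.

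**Conclusion.** The point holds in a limited form. As written, every continuous moderator test in Aim 5 addresses within-school moderation only, and between-school moderation cannot be detected. For severity scores with a low ICC (0.04 to 0.10) the price is moderate: 25% to 30% of the variance and about 10 points of power. For the Area Deprivation Index it may be large: at ICC 0.50 to 0.70, 61% to 77% of the variance is lost and power falls from 49% to 26%, or from 47% to 18%.

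These sizes rest on assumed moderator ICCs and an illustrative interaction of 0.25. The only ICC in the document, 0.04, is for outcomes. That deprivation varies mainly between schools is inferred from the planned spread in subsidized lunch rates and is not stated. The issue is confined to one exploratory aim and leaves Hypotheses 1 and 2 untouched.

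**What to change.** Keep the planned term, within-school deviation × treatment. Add the school mean of the moderator and school mean × treatment, at least for the Area Deprivation Index and any socioeconomic measure treated as continuous. Report both interactions with confidence intervals. State that the 25th, 50th and 75th percentiles are those of the raw scale. Because the model then has two moderator terms, also state the school mean at which each effect is evaluated, for example the overall mean.

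This needs a few lines of wording and code and no new data, and it removes nothing the plan already estimates. The cost is two more parameters per model and a between-school term that will be imprecise with 30 schools: 22% power in the between-only setting above. That term is also a non-randomized comparison of kinds of school, so it may reflect other school differences and should be described as such. Grand-mean centering alone would be simpler, but would not separate the two effects.
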